### Participants

Participants are male and female adolescents aged 12–18 who present in hospital for treatment of a restrictive eating disorder and at least one caregiver. Only adolescents who have not had prior multidisciplinary treatment for an eating disorder will be included. Inclusion and exclusion criteria are summarized in Table 3.^1^ The total enrollment is anticipated to be 60 adolescents.

**Table 3 Tab3:** Inclusion and exclusion criteria

Inclusion criteria	Exclusion criteria
• Adolescent is between 12 and 18 years of age and living at home with caregiver(s) • Adolescent meets diagnostic criteria for anorexia nervosa (either restricting or binge/purge subtype), or sub-threshold anorexia nervosa according to the DSM-5 criteria • Parent or primary caregiver is willing to participate in CRT + TTP or CRT + FFT sessions (if randomized to either condition) • Consent of all family members who will be participating in treatment • The adolescent is not currently receiving outpatient treatment for the eating disorder (i.e., their first presentation at CHOP)	• Caregiver or adolescent with a co-morbid diagnosis of psychotic disorder, substance dependence, substance abuse, or bi-polar disorder • Caregiver or adolescent with diagnosis of intellectual disability, developmental delay, or autism spectrum disorder • Adolescent with a diagnosis of feeding or eating concerns not elsewhere classified with primary symptoms of bingeing and purging, bingeing without compensatory behaviors, or spitting food with restricting patterns. • Adolescent with diagnosis of avoidant/restrictive food intake disorder • Adolescent or caregiver with acute suicide risk • Concurrent psychosocial treatment for another condition • Adolescent or parent (who will be participating) not fluent in English

### Study design

This is a pilot and feasibility study for a randomized controlled trial that is prospective in nature and pragmatic in its approach. The study uses a randomized, three-group design (control, experimental, and contact control) with five assessment time points: baseline (upon admission to hospital for medical stabilization), pre-discharge (the day of, or the day before they leave the hospital), 4 weeks post-discharge, 3 months post-discharge, and 6 months post-discharge. Figure 1 outlines the study flowchart and timetable for data collection.

**Fig. 1 Fig1:**
[figure not shown]
Study flowchart/timetable for data collection

After consent is obtained and baseline assessment is completed, participants are randomized to one of three groups: CHOP’s standard care (treatment as usual; TAU), CRT + contact control (known as “Family Fun Time”), and CRT + Teach the Parent. Those randomized to one of the CRT conditions will receive individual sessions of CRT daily (excluding weekends) while in hospital. Follow-up will be naturalistic. All attempts will be made to follow participants whether they enter outpatient treatment or are referred to a higher level of care. Psychosocial, neurocognitive, medical, and behavioral measures will be collected throughout the study. Group differences will be evaluated at each of the five assessment time points.

### Recruitment and screening procedures

Potential participants are identified during the first 48–72 h after hospitalization for medical stabilization due to malnutrition. Initial screening occurs via review of the electronic medical record. Participants who appear eligible are approached by research assistants and the study and eligibility criteria are described. They are provided with information about the clinical trial (there are currently no other intervention studies and alternatives to participation is treatment as usual), are provided with detailed information regarding the study logistics, and are able to ask any questions. If interested, parents provide consent for themselves and the child provides assent. Adolescents who are 18 years of age provide consent for their participation. Consent ideally occurs within 12–24 h of being informed of the trial and expressing an interest in participating. Study procedures do not take place during meal times, family time, or while visitors are present.

### Description of investigational intervention

The principles of cognitive remediation therapy are the same across studies; however, CRT protocols often vary in terms of the tasks used. This trial uses a modified version of an adolescent manual developed by [name] [47]. The CRT tasks included in our manual are delineated in Table 1. CRT sessions occur daily (excluding weekends) for 45–60 min every day while adolescents are in hospital, for up to 8 days. We have set an a priori definition of “treatment completion” as six sessions of CRT. Treatment completion for parent involvement component was set a priori at three sessions of either TTP or FFT. Though the median length of stay in hospital is 10 days, it is possible that adolescents may discharge before completing all sessions of CRT. These adolescents will continue to complete all study procedures (i.e., follow-up) but will not be considered treatment completers for feasibility assessment (what percentage of adolescents complete CRT) or data analysis (secondary goals).

Study interventionists include the PI or a graduate student under the PIs supervision. [name] provided initial training in CRT, and will provide supervision and feedback to the PI throughout the study duration. CRT sessions will be audio-recorded and coded for adherence to the manual. Should a study interventionist deviate from the manual (e.g., do tasks out of order), this will be noted in the data set. The interventionist will be informed and further training provided to ensure adherence.

CRT sessions are administered every weekday while the adolescent is in hospital, are conducted in an individual format, and tasks are delivered in a standard order to ensure consistency. Table 1 lists all tasks in the standardized order in which they are presented each session. Table 1 also notes the session in which the task occurs; most tasks are administered in each session. It is possible that not all tasks will be able to be administered due to time constraints or individual variables (i.e., hand flip if the adolescent has an IV). At the end of the pilot study, we will re-evaluate the tasks and determine if all should be included a final manual.

Each task has a variety of levels that the adolescent moves through progressively. A particular level of task is repeated in subsequent sessions if the adolescent has difficulty with it. They move to the next level of that task only when they have mastered the current level. For example, each CRT session uses a progressively more difficult version of the Stroop task (e.g., BIG/little—reading the word versus saying “big” if written in uppercase and “little” if written in lower case versus the same type of task using SMALL/large). If the adolescent has difficulty with the Stroop task, they complete the same level of the task until they have mastered it. In the next session they move to the next level of the task. Thus, it is possible that an adolescent can progress through a new level of task each session, yet repeat the same level of a task for a different session (note, the task level is recorded by the interventionist each session).

After each task, the adolescent and study interventionist discuss the process by which the adolescent completed the task. Meta-cognition is fostered and the adolescent is asked to think about real life examples that mirror what was done in session. A series of standardized prompts are used to the guide the discussion, though not all prompts may be necessary in order to generate a discussion. The eating disorder is not discussed unless touched upon by the adolescent. When appropriate, connections to in hospital behavior can be drawn. Between sessions, homework and behavioral tasks are assigned to participants so they can practice what they are learning in CRT. Starting with session 2, the session begins with homework review prior to the CRT tasks.

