### Outcomes

The primary aim of the study is to evaluate the feasibility and pilot the procedures for an RCT of CRT with a family component delivered during a hospital stay for medical stabilization. Primary outcomes are as follows:Recruitment rates (% of patients admitted who are eligible, % enrolled). Ideally, we will be able to recruit 30% of those eligible and at least four adolescents and their parents a month.Completion rates (% of those enrolled who complete at least 6 sessions). Completion rates will vary based on the medically dictated hospital stay. As we have no control over when an adolescent will be discharged, completion rates will be combined with enrollment rates to determine how many participants would need to be enrolled in a future study (over-enrollment) to ensure the appropriate number of treatment completers.Refusal rates and reasons whyRetention rate (% of those enrolled who completed all assessment points, rate of drop out over 6 months of follow-up). Ideally, we would have a dropout rate < 25%. As adolescents are discharging to various levels of care, we track dropout rates and determine if we have higher rates associated with certain levels of care (e.g., residential treatment).Average length of time to complete measures

We will also pilot procedures and evaluate the following:Ease of record forms (can the study staff use forms effectively and can the interventionist easily record data needed from each CRT session)CRT task adaptations (e.g., are some tasks more difficult for adolescents, are there modifications that need to be made)Staffing needs (are there enough staff to recruit/enroll/assess/and administer CRT?)Acceptably of RCT to medical staff (evaluated through meetings with and feedback from staff (e.g., physicians, nurses, behavioral health)

In addition to piloting the study and assessing feasibility, our secondary goals are to examine relevant outcomes for a fully powered trial. We will examine the following:Willingness of adolescent to engage in treatment post-dischargeAdolescent rate of weight gain post-discharge to 6 monthsParental accommodation in symptoms post-discharge (group differences and over time changes)Changes in set-shifting or central coherence

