#### Efficacy analysis

Although this is a pilot study, we do want to explore whether or not there is a difference between groups. In order to determine differences between those who are randomized to TAU, CRT + FFT, or CRT + TTP, we will conduct a mixed multivariate analysis of variance (MANOVA) with five repeated measures (time: baseline, discharge, 4 weeks post-discharge, 3 months post-discharge, and 6 months post-discharge) as a within-subjects factor and treatment as a three-level between subjects’ factor. We will also evaluate the condition (treatment) × time interaction. We have three quantitative dependent variables: adolescent treatment engagement, post-treatment weight gain, and symptom accommodation. For initial analyses, we will focus on change pre- to 4-week post-discharge. Any post hoc comparisons will involve comparing subsequent assessments to baseline—as they will be simple planned comparisons. This will allow us to retain the most amount of power (i.e., to enable us to reject the false null hypothesis) [57]. We will also set alpha at .10, which will also increase power. Given these parameters, enrolling 60 adolescents would give us an N comparable to prior research using CRT [58].

In addition to the prior analyses, we will also assess developmental trajectories for rate of weight gain post-discharge, treatment engagement post-discharge, and symptom accommodation using latent growth curve modeling (LGCM) with one growth curve analysis for each variable. LGCM is a structural equation modeling method that models repeated observed measures (measured variables) on factors (latent variables) representing random effects [59]. In LGCM, a level factor is used to represent baseline and trend factors are used to represent rate of change across time. Latent variables define the form of rate of change across time (e.g., linear, quadratic, cubic). Factor loadings are fixed to define baseline level and trend. For a linear trend, the factor loadings are set so they increase uniformly with each unit increase in time. Given is a preliminary analysis, these results will allow us to better understand how change occurs over time. Instead of relying on probability values which subject us to increased type II error rates given the small sample size (i.e., low power), we will assess confidence intervals around our estimates to provide information regarding margins of error. All confidence intervals will be 90% confidence intervals given the small sample sizes.

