## Discussion

The current study is a pilot and feasibility study that examines the implementation of CRT on a medical unit in a large children’s hospital. The description of this protocol followed SPIRIT guidelines [53, 54]. CRT + TTP is compared to treatment as usual and a CRT + contact control group (CRT + FFT). As this is a pilot and feasibility study, we have specified the outcomes we would use in a larger, randomized clinical trial. We plan to focus on the viability of integrating CRT into clinical care, refine recruitment procedures and estimate recruitment rate for a larger trial, and pilot the feasibility of the assessment strategy. Inpatient hospitalization presents as a unique opportunity for us to examine our primary outcomes of interest and establish the feasibility of this type of intervention in the context of a medical unit. Scaling this study up for a larger trial will be feasible if CRT is able to be delivered with little interruption to clinical care, if study interventions are not perceived as burdensome to staff or families, and if participants are able to be successfully recruited and retained through the follow-up phase. By evaluating our rate of enrollment and follow-up and the % of treatment completers, we should be able to determine how long it would take to enroll enough treatment completers to have a fully powered trial. If it would take 3+ years to recruit enough participants from one site, we would need to consider if it feasible to scale up the study or if a multi-site study is needed. The secondary aims could help to inform this—particularly if we see trends in a positive direction. If there is no trend for a difference between TAU and the experimental groups on secondary outcomes and it would take a two-site study to complete, scaling up of this work may not be feasible.

The study intervention builds upon prior research on the use of CRT as an adjunctive treatment for AN. In particular, this study uses CRT as a pre-treatment intervention. While increases in cognitive flexibility are typically the primary outcome of CRT, we posit that CRT may be particularly useful in increasing willingness to engage in treatment upon discharge from the hospital. In addition to assessing stages of change, we are also examining the rate of weight gain when discharged.

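### The intervention section ties the secondary-outcome analysis to completing six CRT sessions, while the efficacy and power sections analyse everyone randomised; a completer restriction would expose the CRT-versus-TAU contrasts to selection bias

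*Protocol article*

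**What the plan says.** **Description of investigational intervention.** Completion of the adolescent intervention is defined in advance "as six sessions of CRT", out of up to eight. The parent component has its own threshold: "Treatment completion for parent involvement component was set a priori at three sessions of either TTP or FFT". The section accepts that some adolescents will be discharged before all sessions are done. It then says two things about them: "These adolescents will continue to complete all study procedures (i.e., follow-up"), but they "will not be considered treatment completers for feasibility assessment (what percentage of adolescents complete CRT) or data analysis (secondary goals").

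**Efficacy analysis.** The purpose of the mixed MANOVA is to "determine differences between those who are randomized to TAU, CRT + FFT, or CRT + TTP". No completer restriction appears here.

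**Power analysis.** The MANOVA power of .55 is for three groups of 20. The growth-curve simulations are for a sample of 60.

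**Outcomes and Discussion.** "Completion rates will vary based on the medically dictated hospital stay", and the investigators do not control discharge. For the later trial, enrolment and completion are to be used to "determine how long it would take to enroll enough treatment completers to have a fully powered trial".

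**Treatment at usual.** The control arm receives no experimental intervention, so no completer status can be defined in it.

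**The concern.** The intervention section gives completer status a role in the analysis of the secondary goals and names no such role as covariate, subgroup or sensitivity analysis. The efficacy and power sections have no place for it. A reader cannot tell from the article which adolescents enter the main comparison of engagement, weight gain and parental accommodation.

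The answer matters because completion is a post-randomisation event that depends on length of stay and exists only in the two CRT arms. If short-stay adolescents leave the CRT arms while short-stay TAU adolescents remain, any link between length of stay and later outcome shows up as a CRT effect. The direction is unknown: if longer-stay adolescents do worse after discharge, a real benefit is masked; if they do better, one is manufactured.

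The Discussion gives these contrasts some weight. The absence of a trend between TAU and the experimental groups, together with the need for a second site, would count against scaling up. A selection artefact could create or hide that trend.

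Two smaller uncertainties compound this. The early-discharge sentence concerns adolescents who leave before all sessions (up to eight), whereas completion is six. It is also unclear whether the three-session parent threshold bears on the analysis set.

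**Working it through.** **1. Reproduce the stated power.** Inputs from Power analysis: k = 3 groups, m = 5 occasions, N = 60, f = .25, alpha = .10. Repeated-measures MANOVA, group-by-time interaction, Pillai trace, noncentral F:

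- s = min(k − 1, m − 1) = 2
- df1 = (k − 1)(m − 1) = 2 × 4 = 8
- df2 = s(N − k − (m − 1) + s) = 2 × (60 − 3 − 4 + 2) = 110
- lambda = f² × s × N = 0.0625 × 2 × 60 = 7.5
- power = .551, against .55 stated

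The stated figure therefore counts all 60 adolescents and assumes that nobody is set aside.

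**2. Power if CRT non-completers were dropped.** All 20 TAU adolescents stay and each CRT arm keeps 20 × c, so N = 20 + 40c. The completion rate c is an assumption. Effect size f is held fixed, and total N is used although the groups become unequal, so these values are approximate.

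| c | N | power |
|---|---|---|
| 100% | 60 | .55 |
| 90% | 56 | .52 |
| 80% | 52 | .49 |
| 70% | 48 | .46 |
| 60% | 44 | .42 |
| 50% | 40 | .39 |

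**3. Is low completion plausible?** The article gives a median stay of 10 days, identification within the first 48–72 hours, consent and baseline neuropsychological testing before randomisation, and sessions on weekdays only. Suppose the first session falls on hospital day 4 (assumption). Days 4 to 10 are seven consecutive days and hold exactly five weekdays, even counting the day of discharge; that is one short of six. From day 3 there are eight consecutive days, which hold five or six weekdays. Completion near or below 50% is therefore possible, though the article states no rate.

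**4. Bias with no treatment effect.** Let r be the correlation between length of stay and outcome (assumption), and let completers be the fraction c of CRT adolescents with the longest stays. With both variables standard normal, the spurious CRT-minus-TAU difference is r × φ(t)/c SD, where t = Φ⁻¹(1 − c).

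- c = 50%: t = 0 and φ(t)/c = 0.798. For r = 0.2, 0.3 and 0.5 the bias is 0.16, 0.24 and 0.40 SD.
- c = 80%: φ(t)/c = 0.35. For r = 0.3 the bias is 0.11 SD.
- r = 0: no bias at any c.

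**5. Type I error at nominal .10.** Simple two-group comparison, pooled CRT completers against TAU. At c = 50% there are 40 × 0.5 = 20 completers against 20:

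- SE = sqrt(1/20 + 1/20) = 0.316 SD
- rejection probability = P(|Z + bias/SE| > 1.645)
- r = 0.2, 0.3 and 0.5 give .14, .20 and .35

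A simulation of the two-sample t test, in which the number of completers varies, gives .145, .197 and .358. At c = 80% and r = 0.3 it gives .128; at r = 0 it stays near .10.

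**The case against.** The strongest reply is that no sentence excludes anyone. The intervention section withholds a label, which would also fit coding completer status as a variable or running a secondary completer analysis. The sections that actually describe the analysis point to all randomised adolescents: the efficacy section names the arms as randomised, the power figure needs all 60, and early-discharged adolescents are kept in follow-up. This stands to the extent that exclusion cannot be presented as the stated plan. It does not remove the problem, because the article gives completer status a place in the secondary analysis, assigns it no other use there, and nowhere reconciles this with the efficacy section. That is a conflict within the article itself, not a detail that one would expect an unseen analysis plan to supply.

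A reader might also infer that randomisation is broken throughout. The article does not support that. TTP and FFT share the six-session and three-session thresholds, so a restriction would apply to both alike; their contrast would be exposed only if stay or attendance differed between those two arms. The one-sided selection concerns contrasts with TAU.

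Nor do the references to completers in Outcomes and Discussion define this trial's analysis set. They concern enrolment planning for a later trial, and at most make the completer reading more natural.

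Finally, the magnitudes rest on an assumed completion rate and correlation, and the error rates are for a two-group test rather than the planned three-group MANOVA. That is correct, and they should be read as illustration.

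**Conclusion.** The concern holds as a conflict about the analysis population, with a conditional risk of bias. The intervention section, on its natural reading, ties the secondary-outcome analysis to completers; the efficacy and power sections assume everyone randomised. If the completer reading were applied, the CRT-versus-TAU contrasts would lose the protection of randomisation.

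How far they would be distorted cannot be known from the article. Under the assumptions shown, it ranges from nothing (no stay-outcome correlation), through a small distortion at 80% completion and correlation 0.3, to a type I error about three and a half times the nominal level at 50% completion and correlation 0.5. Power, already .55, would fall under any such restriction.

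Severity is moderate. The affected aims are secondary and preliminary in a feasibility pilot, and the primary feasibility rates are untouched. The point still deserves correction because the trend between TAU and the experimental groups feeds the scale-up decision.

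**What to change.** In Description of investigational intervention and in Efficacy analysis, state that the main analysis of all secondary outcomes includes every randomised adolescent in the assigned arm, regardless of the number of CRT or parent sessions attended. Limit completer status to two uses: the feasibility completion rate, and a sensitivity analysis labelled as such and reported with the caveat that TAU has no matching subset. The same sentence should say whether completion there means six CRT sessions alone or also three parent sessions.

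The cost is wording only. Early-discharged adolescents already continue in follow-up, so no new data are needed, and the stated power of .55 is unchanged. The downside is that the estimated effect may look smaller, because adolescents who received few sessions are included.
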